| The exclusion criteria will include   1. presence of small cell, neuroendocrine or ductal differentiation at needle biopsy of the prostate gland 2. individuals with prior pelvic irradiation therapy for any form of pelvic malignancy 3. patients with psychiatric conditions requiring anti-psychotic therapy, or preventing the provision of informed consent 4. renal impairment with serum creatinine more than twice the upper limit of normal 5. Other prior malignancy less than or equal to 5 years prior to recruitment 6. ECOG performance status 2 or poorer |
| Subject Replacement |
| There will be an attempt to replace subjects who drop out of the study. |
| **STUDY DESIGN** |
| This is a single arm phase II study in a single centre in Singapore.  Upon recruitment, all patients will undergo oral administration of ARN 509 (apalutamide) 240mg once daily for 12 weeks. This is followed by standard of care radical prostatectomy within 4 weeks of the last dose of ARN 509.  The details of visits and research related activity schedule is listed in Table 1. |
| There will be no video recording of these procedures. |
| Randomisation and Blinding |
| There is no randomisation or blinding in this study. |
| Contraception and Pregnancy Testing |
| If the study subject is engaged with sexual activity with a woman of childbearing potential, he should use contraception in the time period during and up to 3 months after the last administered dose of ARN 509. |
| Study Visits and Procedures |
|  |
| Screening Visits and Procedures |

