| All potential subjects are referred from their primary urologists. They will be screened by a member of the study team, and the procedure will include:   1. a detailed history and clinical examination 2. screening investigations including FBC, renal panel. liver panel, thyroid function, urinalysis, PSA, hepatitis screen, chest X ray and ECG   These screening tests should be done after clinical eligibility is ascertained and the recruitment into the trial should occur within 4 weeks of screening.  In addition to the blood samples taken for screening, peripheral blood will be collected at the following occasions: (i) during trial entry, at the completion of ARN 509 therapy timed together with pre-operative blood tests, and after surgery timed together with post surgery PSA assessment About 50ml of blood will be taken at each venepuncture. A total of 175 ml for all study related blood tests is expected.  Voided urine about 150ml will be taken at the same timing as peripheral blood. A total of 470ml of urine will be expected to be collected.  These samples may be tested for the following, inclusive but not limited to proteomics, genetics and cytokines testing.  The samples will be retained at the end of the study by the investigator and stored in a secure room in SGH. Only the study team will have access to the study samples. In the event the samples are required to be transported outside SGH to a service provider, these samples will be coded.  The subject can withdraw consent to participate in the sample collection and/or for their samples to be retained at any time and still continue with the study.  Sample analysis is restricted to purposes of this study and not for future unknown usage. |
| Study Visits and Procedures |
| The following are scheduled during the intervention phase of the study:   1. week 0 where patients will receive ARN 509 2. week 4 after commencement of ARN 509 for clinical consult, physical examination and QoL outcomes 3. week 12 at completion of ARN 509 treatment, where clinical examination, blood investigations, QoL outcomes and adverse effects monitoring is performed 4. Standard of care surgery by week 16 5. Final visit at weeks 20-24 for a clinical examination, QoL outcomes, adverse effects monitoring and serum PSA assessment |
| Final Study Visit: |

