| The final study visit is about 4-6 weeks after standard of care surgery, where clinical examination, QoL outcomes measurement, adverse effects monitoring and serum PSA will be ascertained. |
| Post Study Follow up and Procedures |
| A post study follow-up is planned only for individuals who have drug related adverse effects that are present at the initial study visit. These patients will be monitored until resolution of adverse effects. |
| **TRIAL MATERIALS** |
|  |
| Trial Product (s) |
| This information is provided in section 4 (Effects in Humans) of the Investigator’s brochure which is attached.  Apalutamide is not marketed in Singapore, and the use of the study drug will be followed as per protocol. |
| Storage and Drug Accountability |
| The product comes as 60mg tablet stored in high density polyethylene (HDPE) bottles with child-resistant closures (CRC) and tamper-proof heat induction seals.  They are to be stored at room temperature in lock and key. |
|  |
| **TREATMENT** |
| Rationale for Selection of Dose |
| Preceding phase I and II studies have determined a daily dose of 240mg is efficacious and safe ( See Investigator Brochure Section 4.2 and Appendix B.1) |
| Study Drug Formulations |
| They will be dispensed as tablets to be stored at room temperature. |
| Study Drug Administration |
| The study drug should be taken once in the morning with or without food. |
| Specific Restrictions / Requirements |
| The following drugs should be stopped during the study period when ARN 509 is being consumed:   - Aminophylline/theophylline -  Atypical antipsychotics (eg, clozapine, olanzapine, risperidone, ziprasidone) -  Buproprion -  Lithium -  Meperidine and pethidine -  Phenothiazine antipsychotics (eg, chlorpromazine, mesoridazine, thioridazine) -  Tricyclic and tetracyclic antidepressants (eg, amitriptyline, desipramine, doxepin,   imipramine, maprotiline, mirtazapine) |
| Blinding |
| Not applicable. |
| Concomitant therapy |
| All medications (prescription and over the counter), vitamin and mineral supplements, and / or herbs taken by the participant should be documented. |
|  |
| **SAFETY MEASUREMENTS** |
| Definitions |

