| All SAEs that are unexpected and related to the study drug will be reported to HSA. All SAEs will be reported to HSA according to the HSA Guidance for Industry “Safety Reporting Requirements for Clinical Drug Trials.”  The investigator is responsible for informing HSA no later than 15 calendar days after first knowledge that the case qualifies for expedited reporting. Follow-up information will be actively sought and submitted as it becomes available. For fatal or life-threatening cases, HSA will be notified as soon as possible but no later than 7 calendar days after first knowledge that a case qualifies, followed by a complete report within 8 additional calendar days. Safety Reporting Requirement for Johnson & Johnson & Johnson All AEs will be recorded from the time the patient signs informed consent to 28 days after the last dose of the study drug(s). AEs and SAEs will be recorded on the AE page of the CRF and in the patient’s source documents. All SAEs must be reported to Johnson & Johnson within 24 hours of the study site staff’s knowledge of the event, using the Johnson & Johnson SAE Report Form. |

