| The study team members will perform the safety monitoring in this study.  Upon recruitment, all patients will be given the contact number of the PI which is accessible 24 hours. They will be instructed to report all suspected adverse effects within 24 hours of occurrence to the PI.  The scheduled collection of safety data will occur at weeks 6 and 12 and 20-24 after initiation of ARN 509, where a study team member will enquire about possible adverse effects experienced by the subjects.  A 6 monthly review of the safety data and of the collected study data will be performed by the study team.  Please include details on the Data Safety Monitoring Plan (DSMP) for the research study. Please discuss the plans in place to ensure the safety and well being of subjects, and integrity of data collected. |
| Complaint Handling |
| All complaints will be directed towards the Director, Division of Research, Singapore General Hospital.  The complaints will be investigated in conjunction with inputs from the Principal Investigator.  The details of all complaints will be recorded and kept confidential. |
|  |
| **DATA ANALYSIS** |
| Data Quality Assurance |
| The source data will be the case records and all data entries will be cross-checked by the PI after data entry and prior to data analysis. |
| Data Entry and Storage |
| Data will be kept encrypted and electronically within a SGH network computer secured with a user password and room secured with card access. |
|  |
| **SAMPLE SIZE AND STATISTICAL METHODS** |
| Determination of Sample Size |
| There is historical study data showing no more than pathological down staging of 15% in neoadjuvant studies with conventional androgen deprivation.  Phase II studies in advanced prostate cancer patients show a 89% reduction of PSA levels of 50% or more in patients previously treated with conventional androgen deprivation.  For this study with treatment naïve patients, we extrapolate that the study drug will exert a conservative effect equivalent to 40% of patients with significant tissue response with low residual disease burden.  Using a one sided P value of 0.05, beta of 0.2, a single arm study of about n=30 patients will be required. |
| Statistical and Analytical Plans |
| - - - 1. General Considerations   As this is a single arm study with no control group, all analysis will be performed with the intent of characterising outcomes in this group, so as to form the background for future related interventional studies. |

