| - - - 1. Safety Analyses   Drug related adverse effects will be graded according the CTCAE grading scale. All AEs reported will be graded according to scale and the prevalence calculated. |
| - - - 1. Interim Analyses   An interim analysis of outcomes will be performed when 50% accrual is completed.   - - - 1. Describe the types of statistical interim analyses, including their timing.   This will be performed when 50% accrual is completed, and will include:   1. safety outcomes analysis 2. study primary and secondary objectives as listed |
| **DIRECT ACCESS TO SOURCE DATA/DOCUMENTS** The investigator(s)/institution(s) will permit study-related monitoring, audits and/or IRB review and regulatory inspection(s), providing direct access to source data/document. **QUALITY CONTROL AND QUALITY ASSURANCE** The collected data will be compared with the source data ( patient case records). This will be cross checked by at least 2 members of the study team. The access to the data will also be maintained under lock and key and only accessible to the PI and co-PIs.  Evaluation of data quality is every 6 months.  The PI and co-investigators would perform the data and safety monitoring. **ETHICAL CONSIDERATIONS** This study will be conducted in accordance with the ethical principles that have their origin in the Declaration of Helsinki and that are consistent with the Singapore Good Clinical Practice and the applicable regulatory requirements.  This final study protocol, including the final version of the Patient Information and Informed Consent Form, must be approved in writing by the Centralised Institutional Review Board (CIRB) and regulatory approval from Health Sciences Authority (HSA), prior to enrolment of any patient into the study.  The principle investigator is responsible for informing the CIRB and HSA of any amendments to the protocol or other study-related documents, as per local requirement. |
| Informed Consent |
| The consent will be obtained after the patient is aware of his diagnosis and has consented to undergoing radical prostatectomy for prostate cancer.  Consent will be obtained by PI and co-PIs, and will be taken in the outpatient clinic. This is the most common location where patients are told of their diagnosis and counselled for surgery.  Patients will be told that their treatment and follow-up will not be influenced by their decision on enrolment into the study.  We will recruit English speaking patients. There will be no minors. |

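### The protocol's only AE recording window closes at week 16 for a completer, before the weeks 20-24 visit at which AEs are still to be collected

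*Protocol*

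**What the plan says.** **Recording window.** Section 7.3, in the part on the funder's safety reporting requirement, says "All AEs will be recorded from the time the patient signs informed consent to 28 days after the last dose of the study drug(s"). The next sentence says where entries go: "AEs and SAEs will be recorded on the AE page of the CRF", and also in the source documents. No other start and end for AE recording is given.

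**Dosing and surgery.** The Study Design section sets 12 weeks of daily dosing. "This is followed by standard of care radical prostatectomy within 4 weeks of the last dose of ARN 509". The visit list puts surgery no later than week 16.

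**Safety collection after surgery.** The visit list has "Final visit at weeks 20-24 for a clinical examination, QoL outcomes, adverse effects monitoring and serum PSA assessment". The Safety Monitoring Plan (7.4) agrees on the last time point: "The scheduled collection of safety data will occur at weeks 6 and 12 and 20-24 after initiation of ARN 509". Table 1 marks AE monitoring at surgery and at weeks 20-24, and gives surgical complications a row of their own at the same two points. The Study Design section makes Table 1 the reference: "The details of visits and research related activity schedule is listed in Table 1".

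**A second date for the final visit.** The Final Study Visit section says "The final study visit is about 4-6 weeks after standard of care surgery", again with adverse-effect monitoring.

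**Use of the data.** The first secondary objective is the rate of CTCAE events of grade 3 or worse, with no restriction to drug-related events. Under Safety Analyses, "All AEs reported will be graded according to scale and the prevalence calculated".

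**The concern.** The protocol gives a closing date for AE recording and also schedules AE collection after that date, without saying which governs the CRF. A site could ask about events at weeks 20-24 and still regard a new one as outside the recording window.

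The cut-off is awkwardly placed for this trial. The surgery limit and the recording limit are both 28 days after the last dose, so the later a man is operated on, the less of his post-operative course is recorded. The hypothesis concerns the safety of the drug combined with prostatectomy, so the weeks after surgery belong to the safety question. The exposed quantity is the post-operative part of the grade 3+ AE rate. The amount of post-operative time in that rate would be set by theatre scheduling.

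**Working it through.** This is calendar arithmetic. No event rate or onset time is assumed.

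**Inputs**
- Dosing lasts 12 weeks (Study Design), so the last dose for a completer is at 12 × 7 = day 84.
- Surgery is at most 4 weeks after the last dose (Study Design).
- AE recording ends 28 days after the last dose (section 7.3).
- The final visit is at weeks 20-24 (visit list, Appendix 1, Table 1), or about 4-6 weeks after surgery (Final Study Visit).

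**The protocol's own figure.** Latest surgery = 84 + 28 = day 112 = week 16, as the visit list states.

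**End of AE recording.** 84 + 28 = day 112 = week 16, the same day.

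**Gap to the final visit**
- Weeks 20-24 schedule: 7 × (20 − 16) = 28 days to 7 × (24 − 16) = 56 days, for every completer.
- 4-6 weeks after surgery at week S: S + 4 − 16 to S + 6 − 16 weeks. This is 0-2 weeks at S = 12 and 4-6 weeks at S = 16, so 0-6 weeks overall.

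**By surgery week S**
- Post-operative days recorded under section 7.3 = 7 × (16 − S). The share is of the first 28 post-operative days.
- Post-operative days up to the scheduled visit = 7 × (20 − S) to 7 × (24 − S).
- The two visit rules share dates only if S + 6 ≥ 20, that is S ≥ 14.

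| S | Days recorded | Share of first 28 | Days to weeks 20-24 visit | Visit 4-6 weeks after surgery | Dates shared by both rules |
|---|---|---|---|---|---|
| 12 | 28 | 100% | 56-84 | weeks 16-18 | none |
| 13 | 21 | 75% | 49-77 | weeks 17-19 | none |
| 14 | 14 | 50% | 42-70 | weeks 18-20 | week 20 only |
| 15 | 7 | 25% | 35-63 | weeks 19-21 | weeks 20-21 |
| 16 | 0 | 0% | 28-56 | weeks 20-22 | weeks 20-22 |

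**Early stop.** A man whose last dose is at week 8 reaches the cut-off at week 8 + 4 = 12, the start of the surgery period in Table 1.

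**After the fix.** Recording to weeks 20-24 ends 7 × (20 − 12) = 56 to 7 × (24 − 12) = 84 days after the last dose. Post-operative cover is then at least 28 days, even for surgery at week 16.

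**The case against.** The strongest reply is that the sentence states only the funder's window. It stands under the funder's heading, just before the funder's 24-hour SAE rule, and it nowhere says that recording stops. The visit list, the Final Study Visit text, the Safety Monitoring Plan and Table 1 all expect AE monitoring at the final visit. That reading is open, and a reader should not infer that sites are certain to stop CRF entry at week 16. But the sentence covers all AEs, the next one names the CRF page, and the protocol offers no other end date. The ambiguity remains.

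A reader might also infer that post-operative safety data would be lost. The documents do not support that. Case records are the source data, patients are told to report suspected adverse effects to the principal investigator with no end date given, and reporting times to the review board and the regulator run from awareness of the event. Events elicited late could stand in the source even if they were not on the CRF.

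Nor is the surgical complication objective cut short, since its Table 1 row runs to weeks 20-24.

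Finally, Safety Analyses begins with drug-related effects, for which a window tied to the last dose is defensible. That has weight, but its next sentence covers all AEs reported, and the objective itself is not limited to drug-related events.

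**Conclusion.** The inconsistency is real and calls for a minor-to-moderate correction. The only stated recording window closes at week 16 for a completer, while AE collection is scheduled 28-56 days later under the weeks 20-24 schedule. The 4-8 week figure should not be taken as holding on every reading: under the Final Study Visit timing the gap is 0-6 weeks.

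If the CRF follows section 7.3, post-operative recording falls from 28 days to none across the permitted surgery dates, and only the post-operative part of the CTCAE grade 3+ rate is touched. The zero arises only for surgery at the week 16 limit. The protocol gives neither a distribution of surgery dates nor post-operative event rates, so no share of patients and no shift in the rate can be stated. A reader who inferred a biased safety result of known size would go beyond the documents.

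The two final-visit dates are a secondary alignment point. Taken literally they do not overlap for surgery before week 14, though the word about softens the edges. They affect when post-operative PSA and quality of life are read, and neither is named in the objectives.

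**What to change.** 1. In section 7.3, state that 28 days after the last dose is the funder's minimum reporting window. Add that AEs are recorded on the CRF to the final study visit, or to 28 days after the last dose if that is later or surgery is not done.
2. Change the Final Study Visit section to weeks 20-24, to agree with Table 1.

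**Cost.** Amendment wording, and 4-8 more weeks of AE entry per completer at a visit already scheduled. No visits, patients or procedures are added.

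**What it leaves open.** Follow-up after surgery still varies, from 28 days (surgery at week 16, visit at week 20) to 84 days (surgery at week 12, visit at week 24), including for PSA and quality of life. A fixed post-operative counting window could even this out for the AE rate, since every operated completer who attends on schedule would have at least 28 recorded days. That is an analysis definition and can be left to the analysis plan; removing the contradiction does not require it.

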| This is a phase II single arm study to look at efficacy feasibility and safety of neoadjuvant ARN 509 with radical prostatectomy. The outcomes of this study will form the background for subsequent phase III randomised trials. |
|  |
| **HYPOTHESIS AND OBJECTIVES** |
|  |
| Hypothesis |
| The hypothesis is that neoadjuvant ARN 509 combined with radical prostatectomy is a safe and feasible treatment option for organ-confined intermediate to high risk prostate cancer. |
| Primary Objectives |
| 1. Objective – to assess the proportion of patients with pathological downstaging at radical prostatectomy   (ii) Objective – to assess the  oncological efficacy of combination neoadjuvant ARN 509 and radical prostatectomy in primary prostate tumours |
| Secondary Objectives  1. Objective – to the rate of CTCAE grade 3 or high adverse events 2. Objective – to assess the proportion of patients with peri-operative Clavien-Dindo complications grade 3 and above. 3. Objective (exploratory) – to assess the effect of neoadjuvant ARN 509 on apoptosis and androgen signaling of prostate cancer |
|  |
| Potential Risks and Benefits: |
| Potential Risks |
| There have been adverse drug reactions reported in ARN 509 human studies including fatigue, decreased appetite, nausea , constipation, dysgeusia. It is not known if these are directly caused by the study drug.  Seizures have been observed in animals study at very high serum levels of the drug, but not observed in human studies utilising 240mg daily doses. |
| Potential Benefits |

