| The potential direct benefits to participants include:  (i) better long term cancer control when there is synergism between neoadjuvant androgen receptor inhibition and radical surgery  (ii)  better understanding of the clinical efficacy of ARN509 in organ confined prostate cancer will potentially allow wider clinical indications for this new drug.  (iii) with better long term cancer control, there is a lower risk of recurrence and the need for future treatment including prolonged androgen deprivation therapy or radiation therapy  (iv) downstaging of disease in the prostate allows for higher probability of nerve sparing surgery which will lead to better functional outcomes of continence and potency  (v) the background information from this study may allow the study team to progress onto a multi-centre, double-blind, placebo controlled trial which will enhance the care of prostate cancer for patients  The indirect benefits to the participants include:  (i) better understanding of the biological response of human prostate cancer to ARN 509 which will potentially give insight to new therapeutic options |
|  |
| **STUDY POPULATION** |
| List The Number and Nature of Subjects to be Enrolled. |
| This will be a single centre study recruiting n=30 patients. Only male patients between 21-75 years of age will be recruited as this age range represents the surgical cohort predominant in our local practice. |
| Criteria for Recruitment and Recruitment Process |
| Suitable patients will be screened by the study team investigators and recruited in the outpatient clinics in the Singapore General Hospital. |
| Inclusion Criteria |
| The inclusion criteria include   1. those aged between 21 to 75 years of age with histologically diagnosed primary adenocarcinoma of the prostate gland within 6 months of recruitment 2. non-metastatic D’Amico intermediate to high risk patients undergoing radical prostatectomy as primary definitive therapy 3. no known hypersensitivity to the study drug 4. able to swallow study drug as whole tablets |
| Exclusion Criteria |

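### Section 9.1: the stated n=30 and beta of 0.2 do not agree; 15% versus 40% needs about 16 to 22 patients, and 30 gives about 91% power (conservative, minor correction)

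*Protocol*

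**What the plan says.** Section 9.1 (Determination of Sample Size) gives two rates. The reference is "There is historical study data showing no more than pathological down staging of 15% in neoadjuvant studies with conventional androgen deprivation". The expectation for the study drug is a "conservative effect equivalent to 40% of patients with significant tissue response with low residual disease burden". It then concludes: "Using a one sided P value of 0.05, beta of 0.2, a single arm study of about n=30 patients will be required". It names no test or formula, does not call 15% a null value, and states no allowance for dropout.

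The study population section repeats the number: "This will be a single centre study recruiting n=30 patients". Under Subject Replacement, the protocol says that it will try to replace men who drop out. The first primary objective is "to assess the proportion of patients with pathological downstaging at radical prostatectomy". Section 9.2 describes the purpose of the analysis: "all analysis will be performed with the intent of characterising outcomes in this group". It also plans an interim analysis at 50% accrual that includes the primary objectives.

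**The concern.** The sentence in section 9.1 presents 30 as the number that the two error rates require. A reader who puts 15%, 40%, one-sided 0.05 and 80% power into a one-sample calculation gets a clearly smaller number. Either n or beta is therefore not the figure that belongs with the others, or an input has been left out.

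What is at stake is the accuracy of the justification, not the protection that the design gives. The ethics board and the regulator read this sentence to learn why 30 men, and not fewer, are to take an investigational drug before surgery. A later reader will also take 80% as the power of the trial at 40%, when it is higher.

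**Working it through.** **Inputs, all from section 9.1.** p0 = 0.15 (historical downstaging), p1 = 0.40 (expected response), one-sided alpha = 0.05 (z = 1.645), beta = 0.2 (z = 0.842), single arm. Two things are assumed: that 15% acts as the null value, and that both rates describe the same endpoint.

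**Attempt to reproduce n=30.**

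1. Normal approximation with the null and alternative variances:
   n = [1.645·√(0.15·0.85) + 0.842·√(0.40·0.60)]² / (0.40 − 0.15)² = [0.587 + 0.412]² / 0.0625 = 15.99, so **16**. With continuity correction, **20**.
2. Arcsine transformation: 18.76, so **19**.
3. Exact binomial, taking the smallest cut-off r with P(X ≥ r | 0.15) ≤ 0.05:

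| n | r | true alpha | power at 40% |
|---|---|---|---|
| 21 | 7 | 0.0287 | 79.98% |
| 22 | 7 | 0.0368 | 84.2% |
| 24 | 8 | 0.0199 | 80.8% |
| 30 | 9 | 0.0278 | 90.6% |

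The exact requirement is **22**, and every n from 22 to 40 keeps at least 80% power. Thirty is 8 more than 22 (8/22 = 36% above) and 14 more than 16 (14/16 = 88% above).

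**Other routes that were tried.**

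- Variance at p1 only: (1.645 + 0.842)²·0.24/0.0625 = 23.74, so 24; with continuity correction, 28.
- Variance at p0 only: 13; with continuity correction, 17.
- Simon two-stage design at 0.05/0.2: maximum 25 (optimal) or 19 (minimax).
- Figures of 29 to 31 appear only with inputs that the section does not state. Examples are 90% power (arcsine with continuity correction 30, Simon optimal 29), two-sided 0.05 with variance at p1 only (31), or a 20% dropout allowance on 24 (24/0.80 = 30).

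**What n=30 delivers (exact).**

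- A cut-off of 8 of 30 has one-sided error 0.070, above 0.05. A cut-off of 9 of 30 has 0.028. The exact rule is therefore 9 or more.
- Power at 40% is 0.906, so beta = 1 − 0.906 = 0.094. The normal approximation gives 94.5%.
- Power is 77.5% at a true rate of 35% and 80.8% at 36%, so 80% is reached at about 36%.

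These figures are for a single final test, with no efficacy claim at the interim analysis.

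**The case against.** The strongest reply is that section 9.1 says about 30 and names no method, so no particular calculation can be called the wrong one. A formula with the variance taken at p1 and a continuity correction gives 28, and a 20% allowance on 24 gives exactly 30. This stands in part: the documents do not show how 30 was reached, and an arithmetic slip by the authors cannot be proved. But neither route is stated, the first still falls short of 30, and the protocol deals with dropout by replacement rather than by inflation. The section attributes the number to the error rates alone.

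The second reply is that the discrepancy is harmless. That is largely right. At n=30 the exact one-sided error (2.8%) and beta (9.4%) are both inside the stated limits.

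Two stronger readings are tempting. A reader might infer that the trial has no success threshold, because section 9.2 speaks of characterising outcomes and the protocol gives no number of responders. The documents do not support this. The test, cut-off and interval are commonly left to a statistical analysis plan, which is not shown. Sizing a single-arm phase II trial against a benchmark and then reporting estimates is ordinary practice. A reader might also infer that the sample size itself is wrong and should change. It need not, because 30 satisfies both stated limits.

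**Conclusion.** The point holds as a minor correction. On the stated inputs, standard one-sample methods need about 16 (normal) to 22 (exact) patients. Thirty patients give about 91% exact power at 40%, or 80% at about 36%. The stated n and beta therefore do not belong together, and nothing in the protocol explains the difference. The error is in the safe direction.

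The conclusion rests on three assumptions: 15% is the null value, there is one final test, and both rates describe the same endpoint. The last is not secured by the text. The 15% is for pathological downstaging, while the 40% is for a tissue response with low residual disease. Unless the two are the same outcome, no calculation of 15% against 40% is well defined, so the rewritten section must settle this as well as the count.

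**What to change.** Keep n=30 and restate section 9.1. Name the primary endpoint, pathological downstaging, for both the 15% reference and the 40% target, and confirm that 40% is the intended target on that endpoint. Then give the basis, for example:

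> The reference downstaging rate is 15% and the target rate is 40%. With 30 patients, an exact one-sided binomial test rejects 15% if at least 9 of 30 are downstaged (exact alpha 0.028). Power is about 91% at a true rate of 40% and about 80% at 36%. These figures assume no efficacy claim at the 50% accrual interim analysis.

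If 30 was meant to include an allowance for patients who do not reach surgery, state the rate and reconcile it with the rule on replacing dropouts. The protocol gives no such rate, so none should be written in without a source. If the target on downstaging is not 40%, recompute the power for the rate that applies.

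The cost is a few sentences of protocol wording. With the 40% target confirmed, there is no change to patient numbers or procedures.
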